### Defining sexual exposure

In women, the process of CT acquisition from an infected partner, i.e., via sex, is defined based on sexual behaviour data from the detailed and frequent questionnaires and by biomarker assessment. The actual CT status of the partner during follow-up will in most cases be unknown. Hence, the sexual behaviour that is reported during follow-up may also include sex with CT negative partners. The risk estimate for the association between sexual exposure and incident CT detection reflects the risk of transmission given this sexual practice and regardless of the partner's CT status. This will be a good proxy to the actual transmission probability for a given sexual practice in ‘real life’ and is most relevant in the practical care setting where information on sexual behaviour is routinely asked about and registered and partners’ CT status is often lacking. To validate sexual exposure from a man, especially to indicate underreporting, biomarker validation is applied.

### Defining alternate anatomic site exposure

The process of CT anorectal acquisition from her own genital CT infection and vice versa is defined based on the CT test results. Exposure is defined as presence of CT detection at the other anatomic site at the same sampling moment and/or the previous sampling moment. CT typing results are also used to confirm the link between the two detections.

### Treatment failure

A possible reason for CT detection after treatment, other than transmission, may be treatment failure. Whether antimicrobial treatment failure for CT plays a role remains poorly understood [41]. There is no evidence of homotypic anti-microbial resistance and testing for antimicrobial resistance for CT is not routinely available. It will therefore be quite difficult to microbiologically ascertain treatment failure as a reason for CT detection. Still, there is current debate on what is the appropriate treatment for anorectal CT infection [39–41]. Some studies conclude that azithromycin is a suboptimal treatment [28, 30–32], while another study found doxycycline and azithromycin treatments to be equally effective for anorectal CT [29]. In some countries (the Netherlands, Australia, UK), guidelines for anorectal CT treatment have recently shifted from azithromycin 1000 mg single dose to doxycycline 100 mg twice daily for 7 days [36, 37], while in the US these treatments are considered to be equally effective first line treatments [35]. These recommendations reflect concern that azithromycin efficacy for anorectal infections may be less than expected. Yet, there are no robust studies showing conclusive evidence concerning a suboptimal effect of any type of treatment or to prefer one over the other treatment. The current study attempts to inform this debate by analysing the association between treatment and CT detection in a sub analysis.

### Statistical analyses

The main study questions will be answered by analysing the data on the level of episodes. For each incident CT detection, the information of the preceding sample results, and the sexual behaviour information from the preceding 2-week interval, is analysed. Using mixed models, univariate and multivariate logistic regression analyses will be applied to calculate rates of incident CT anorectal and genital detection, controlling for repeated measurements in a person. Thereby, the relative contributions are assessed of sexual exposure and of alternate anatomic site exposure, i.e., sexual transmission and self-infection. This will be done by including different exposures as co-factors and this will also be done comparing categories of sexual exposure, anatomic site exposure, and both exposures compared to no such exposure (see Table 2).

**Table 2 Tab2:** Main regression models in FemCure study

	Exposure categories	Definition in the data^b^	Interpretation^c^ of positive CT test result
Outcome incident genital CT detection			
Model 1	Sexual exposure^a^	Genital sexual exposure (at T_x_)	
	Alternate site exposure	Anorectal CT positive (at T_x_ and/or T_x-2_)	
Model 2	No exposure	No genital sexual exposure (at T_x_) AND anorectal CT negative (at T_x_ and T_x-2_)	Persistence
	Genital sexual exposure only	Genital sexual exposure (at T_x_) AND anorectal CT negative (at T_x_ and T_x-2_)	Sexual transmission
	Anorectal site exposure only	No genital sexual exposure (at T_x_) AND anorectal CT positive (at T_x_ and/or T_x-2_)	Transmission from anorectal site
	Sexual exposure and anorectal site exposure	Genital sexual exposure (at T_x_) AND anorectal CT positive (at T_x_ and/or T_x-2_)	Sexual transmission AND/OR Transmission from anorectal site
Outcome incident anorectal CT detection			
Model 1	Sexual exposure^a^	Anorectal sexual exposure (at T_x_)	
	Alternate site exposure	Genital CT positive (at T_x_ and/or T_x-2_)	
Model 2	No exposure	No anorectal sexual exposure (at T_x_) AND genital CT negative (at T_x_ and T_x-2_)	Persistence
	Anorectal sexual exposure only	Anorectal sexual exposure (at T_x_) AND genital CT negative (at T_x_ and T_x-2_)	Sexual transmission
	Genital site exposure only	No anorectal sexual exposure (at T_x_) AND genital CT positive (at T_x_ and/or T_x-2_)	Transmission from genital site
	Sexual exposure and genital site exposure	Anorectal sexual exposure (at T_x_) AND genital CT positive (at T_x_ and/or T_x-2_)	Sexual transmission AND/OR Transmission from genital site

^a^Based on self-administered questionnaires and semen biomarker assessment

^b^T_x:_ test result at the sampling; T_x-2:_ test result at the sampling two weeks earlier

^c^Strain typing is used to further aid interpretation of the observed positive CT test result, specifically to confirm self-infection (i.e., strain types do not differ between anatomic sites) or persistence (i.e., strain types do not differ over time)

Risks will be expressed by odds ratio‘s and 95 % confidence intervals. Co-factors (such as age, but also treatment-type) will be included in the models to account for their potential role as a confounding factor or effect-modifier in the associations between exposure and CT detection. Also, these co-factors are assessed for their association with CT detection.

Sensitivity analyses will be undertaken by varying the definition of the outcome (primary and secondary outcomes) and by varying the definition of the sexual exposure (e.g., including and excluding sexual practices). By performing a (limited) process evaluation of our study, we will obtain insights in the factors that have affected participation and possible loss-to-follow-up.

In a sub analysis, in which the unit of analysis will be an individual woman (not the 2-week episodes), a head-to-head comparison of the two treatments will be conducted.

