### Study population

The eligible study population is likely to reflect the current STI clinic populations. Eligible are heterosexual women with symptomatic or asymptomatic genital and/or anorectal CT infection, who are not pregnant and 18 years or older. Exclusion criteria are recent reported use of antibiotics, HIV positivity, syphilis and infection with *Neisseria gonorrhoea*. As single anorectal CT is uncommon and around 75-95 % of genital CT positive women also have anorectal CT [13–25], it is expected that of the included women only few will have anorectal CT only. The majority (75 %) expectedly will have anorectal CT in combination with genital CT, and most of the remainder will have genital CT only at inclusion in the study. Treatment occurs according to regular care and international guidelines [35–37]. Women who are anorectally tested in routine care and found anorectal CT positive are treated with a 7-day course of doxycycline 100 mg twice daily with the first dosis being directly observed. All other women receive a directly observed single dose of azithromycin 1000 mg [35–37]; these women tested genitally CT positive in routine care and were either anorectally untested in routine care or were tested anorectally CT negative.

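### Table 2 reads a woman's own other-site result as transmission between sites, although unmeasured causes shared by both sites can produce the same odds ratio

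*Protocol article*

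**What the plan says.** All references are to the Protocol article.

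- **Model.** Statistical analyses: mixed models are planned, in which "univariate and multivariate logistic regression analyses will be applied to calculate rates of incident CT anorectal and genital detection, controlling for repeated measurements in a" woman. Table 2 lists incident genital and incident anorectal detection as two outcome blocks, each with a Model 1 and a Model 2. No joint model of the two sites is mentioned.
- **Exposure.** Defining alternate anatomic site exposure: "Exposure is defined as presence of CT detection at the other anatomic site at the same sampling moment and/or the previous sampling moment". In the genital block this becomes "Anorectal CT positive (at T_x_ and/or T_x-2"; the anorectal block mirrors it.
- **Interpretation.** A positive result with alternate-site exposure only is labelled "Transmission from anorectal site" (or from the genital site). The text says that "the relative contributions are assessed of sexual exposure and of alternate anatomic site exposure, i.e., sexual transmission and self-infection".
- **Safeguards.** "Co-factors (such as age, but also treatment-type) will be included in the models to account for their potential role as a confounding factor". Strain typing is used "specifically to confirm self-infection (i.e., strain types do not differ between anatomic sites"; Table 1 marks typing as done in a subset. The planned sensitivity analyses vary the outcome and the sexual-exposure definition, not the alternate-site term.
- **Unmeasured factors.** Defining sexual exposure says that partners' infection status will mostly be unknown. Treatment failure says that failure will be hard to establish microbiologically.

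**The concern.** The other-site result is not an external exposure. It is the same woman's outcome in the mirror model. A random intercept handles repeated measurements at one site, but it assumes that the woman's effect is unrelated to the covariates. Treatment failure, slow clearance or an untreated partner can raise detection at both sites. The other-site result then marks which women have a high underlying risk, and its coefficient absorbs part of that difference.

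The alternate-site odds ratio is one of the study's two key results. If shared causes inflate it, self-infection gains weight relative to sexual transmission, and that comparison is what the study sets out to make.

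**Working it through.** **1. The plan's own figure.** Numbers and power gives 300-380 women with full data, at least 70% power, 5% significance, detection 15-30% and alternate-site exposure 10-30%. The effect size is described only as relevant, so the power cannot be reproduced. Solving for the odds ratio (OR) that gives 70% power (two-sided 5%, one observation per woman) yields 1.95-2.99 with 300 women and 1.81-2.69 with 380. With several episodes per woman the detectable OR could be smaller. The totals are consistent with 400 recruited: 400 × 0.95 = 380 and 400 × 0.75 = 300.

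**2. The model as read from Table 2.** For woman i at sampling t:

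logit P(genital_it = 1) = a + b1·sex_it + b2·E_it + u_i, with E_it = 1 if the anorectal sample is positive at t or at the preceding sampling.

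The anorectal model has its own effect v_i. If corr(u, v) = ρ > 0, the mean of u_i is higher when E_it = 1 than when E_it = 0, and b2 moves above 0 with no transmission between sites.

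**3. The mechanism by hand (illustrative assumption).** Half the women have 5% detection per sampling at each site and half have 15%. Within a woman the sites are independent.
- P(E = 1): 1 − 0.95² = 0.0975 and 1 − 0.85² = 0.2775; mean 0.1875.
- Detection if exposed: (0.2775 × 0.15 + 0.0975 × 0.05) / 0.375 = 0.124.
- Detection if unexposed: (0.7225 × 0.15 + 0.9025 × 0.05) / 1.625 = 0.0945.
- OR = (0.124/0.876) / (0.0945/0.9055) = 1.36, with no transmission.

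This is before any random intercept. Step 4 shows that adding one does not remove the effect.

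**4. Simulation with true between-site OR 1.0.** Random-intercept logistic model, exposure as written, six 2-week episodes. Latent-scale ICC = σ²/(σ² + π²/3), so SD 0.5, 1 and 1.5 give 0.07, 0.23 and 0.41. ICC and ρ are assumptions; the article gives neither.

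| Women | Heterogeneity | ρ | OR | False positives |
|---|---|---|---|---|
| 300 / 380 | SD 1 | 0 | 1.02 / 0.99 | 6% / 4% |
| 340 | ICC 0.05, detection 5-15% | 0.5 | – | 7-11% |
| 340 | ICC 0.10, detection 10% | 0.5 | 1.17 | 9-15% |
| 340 | ICC 0.20 | 0.5 | 1.30-1.39 | 23-41% |
| 340 | ICC 0.20 | 0.8 | 1.56-1.63 | 55-68% |
| 300 / 380 | SD 1 | 0.5 | 1.39 / 1.38 | 40% / 48% |
| 300 / 380 | SD 0.5 | 1 | 1.24 / 1.25 | 25% / 32% |
| 300 / 380 | SD 1 | 1 | 1.94 / 1.98 | 93% / 97% |

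Ranges span repeated simulations of 120 to 150 runs; the rows with 300 / 380 women used 300 runs. At 150 runs the standard error near 5% is √(0.05 × 0.95/150) = 1.8 points. At detection 5% and ICC 0.20, ρ 0.5, the false-positive rate was lower, at 15%.

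**5. Lagging alone.** With only the preceding other-site result, SD 1 and ρ 0.5, the OR was 1.30-1.31 with 24-26% false positives. The bias shrinks but remains.

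**6. Adding the woman's proportion of other-site positives.** Within-woman OR:

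| Truth | Exposure as written | Lagged only |
|---|---|---|
| No transmission, shared heterogeneity | 0.9-1.07 | 0.97-1.02 |
| Lagged OR 2 | 1.29-1.32, detected 18-20% | 1.82, detected 68% |
| Genital-to-anorectal only (OR 4); genital model, truth 1 | 0.73, rejected 28-29% | 0.78, rejected 16% |
| No transmission, shared shock varying over time | 1.46-1.58, rejected 49-62% | 0.89, rejected 7% |

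The split is usable only with the lagged exposure. Under a true lagged OR of 2 the unsplit model gave 2.5-3.1.

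**The case against.** Four objections carry weight.

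- **Safeguards exist.** Sexual exposure is in the same model, co-factors including treatment type are adjusted for, viability and load serve as alternative outcomes, and the questionnaires ask about partners' testing and treatment. Definition of transmission calls self-infection only likely when strains match. This stands in part. Typing can exclude discordant pairs. But one partner infecting both sites, or failure at both, also gives matching strains, and typing covers a subset. Co-factors remove only what is measured.
- **The model structure is partly inferred.** The article does not use the word separate, and details of the random effects may be in a fuller plan. This stands as a caution. The two outcome blocks, the exposure and its interpretation are nevertheless fixed in Table 2.
- **The split is imperfect.** The woman's proportion uses later samples that the outcome may have caused, and a shared cause can vary between episodes. Step 6 bears this out, so the split supports the reading and does not settle it.
- **A joint two-site model may look like the better remedy.** It was not shown to remove the bias. A bivariate version gave 2.4-2.5 for a true OR of 2. A single common intercept worked only when the sites fully shared the effect and over-corrected otherwise (0.70-0.85 at ρ 0 to 0.5).

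A reader might also infer shared heterogeneity from the statement that "around 75-95 % of genital CT positive women also have anorectal CT". That does not follow. The figure describes infection before treatment, says nothing about incident detection afterwards, and would also arise from true self-infection.

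**Conclusion.** The point holds as a limit on interpretation. The alternate-site OR from Models 1 and 2 measures an association that transmission between sites or a shared cause could produce, and Table 2 names only the first.

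The size is conditional. There is no bias with uncorrelated site effects, and it is negligible to small at ICC 0.05 with moderate correlation. At ICC 0.20 and correlation 0.5-0.8 the OR is about 1.3-1.6 with 23-68% false positives. Only strongly shared heterogeneity produces ORs near 2, the lower part of the range in step 1.

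A reader might go further and infer that the study will overstate self-infection, or that a raised alternate-site OR must be spurious. The documents do not support this. They give neither the ICC nor the correlation between sites, and real transmission may also be present.

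**What to change.** 1. Keep Models 1 and 2 as planned.
2. For both sites, add a pre-specified analysis that uses only the preceding other-site result (T_x-2) as exposure. Split it into the woman's proportion of samplings positive at the other site (between-woman) and that preceding result (within-woman). Report both ORs.
3. In the interpretation column of Table 2, replace "Transmission from anorectal site" and its genital counterpart with: *association compatible with transmission from that site or with a shared cause*.
4. State that the alternate-site OR will not be read as self-infection unless the lagged within-woman OR agrees, and word the comparison of relative contributions accordingly.

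**Cost.** One derived covariate per site and revised wording; no new samples or women. State these downsides in the plan: the within-woman OR is less precise (about 60-70% power at a true OR of 2), is biased downward when infection also passes in the other direction, and does not remove every shared cause that varies over time. It is a supporting analysis and not the sole evidence of transmission.

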### Definition of transmission

Transmission is defined as an observed incident CT detection post-treatment (a) after having sex with a source partner (by self-reported behaviour and biomarker-validation), and (b) when another anatomical source location tested positive, i.e., self-infection. In such cases, self-infection is considered likely when CT strain types do not differ between anatomic sites of a woman. Samples with CT detection that follow a sample with CT detection may represent persistence and are considered not indicative for transmission. In such cases, persistence is considered likely when CT strain types do not differ in a woman over time.

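### Table 2 labels positives in exposed cells as transmission without allowing for the background detection the plan expects, and odds ratios alone do not give the relative contributions it aims for

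*Protocol article*

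**What the plan says.** All references are to the protocol article.

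- **Aim of the models** (Statistical analyses): "the relative contributions are assessed of sexual exposure and of alternate anatomic site exposure, i.e., sexual transmission and self-infection".
- **Route to that aim** (same section): the exposures enter together as co-factors (Model 1), and Model 2 works by "comparing categories of sexual exposure, anatomic site exposure, and both exposures compared to no such exposure".
- **Outputs** (same section): "univariate and multivariate logistic regression analyses will be applied to calculate rates of incident CT anorectal and genital detection", and "Risks will be expressed by odds ratio" with 95% confidence intervals. No risk difference, attributable fraction or other measure of contribution is named.
- **Table 2, Model 2, genital outcome:** the reference cell is "No genital sexual exposure (at T_x_) AND anorectal CT negative (at T_x_ and T_x-2", and a positive there is interpreted as *Persistence*. A positive in the sex-only cell is interpreted as *Sexual transmission*. The other-site-only cell is "No genital sexual exposure (at T_x_) AND anorectal CT positive (at T_x_ and/or T_x-2", and a positive there is interpreted as transmission from the anorectal site. The joint cell is left as and/or. The anorectal outcome mirrors this.
- **Qualifier** (Table 2, footnote c): "Strain typing is used to further aid interpretation of the observed positive CT test result", specifically to confirm self-infection or persistence. Table 1 marks typing as done in a subset.
- **Definition of transmission:** "Samples with CT detection that follow a sample with CT detection may represent persistence and are considered not indicative for transmission".

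**The concern.** By giving the no-exposure cell an interpretation, the plan accepts that incident positives arise without measured sex and without a positive at the other site. Whatever causes them (residual or recurrent detection, treatment failure, sex that was not reported) does not stop when a woman is exposed. Only the excess over the no-exposure risk can be credited to an exposure, yet the interpretation column makes no such allowance.

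The reference label has its own difficulty. The outcome is incident detection, and the Definition of transmission section links persistence to a positive that follows a positive. Reading an incident positive as persistence sits uneasily with that. It also leaves out the under-reporting of sex that the Limitations section admits.

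Finally, a relative contribution depends on the effect of each exposure and on how often it occurs; an odds ratio carries only the first. The study ends in practical recommendations, and the balance between sexual transmission and self-infection bears directly on them.

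**Working it through.** **Inputs from the article (Numbers and power):** sex in a 2-week episode, pS = 20-60%; alternate-site exposure, pA = 10-30%; CT detections 15-30%. The article gives no odds ratio, no reference-cell risk and no figure for the contributions, so there is no stated result to reproduce.

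**Assumptions made here:** the exposures are independent, the exposure ranges apply to the episodes analysed, and, in step 3, detection is per episode and odds multiply in the joint cell.

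**Step 1. What the labels would say if neither exposure had any effect.** Risk is then equal in all four cells, so the share of positives in a cell equals its share of episodes.

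Share labelled transmission in some form = 1 - (1 - pS)(1 - pA):
- lowest: 1 - 0.8 × 0.9 = 28%
- highest: 1 - 0.4 × 0.7 = 72%

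Share in the two single-cause cells, without the and/or cell = pS(1 - pA) + (1 - pS)pA:
- pS 20%, pA 10%: 0.18 + 0.08 = 26%
- pS 20%, pA 30%: 0.14 + 0.24 = 38%
- pS 60%, pA 10%: 0.54 + 0.04 = 58%
- pS 60%, pA 30%: 0.42 + 0.12 = 54%

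This step needs no assumed odds ratio or reference risk.

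**Step 2. Background share within an exposed cell when there is an effect.** With reference risk b and odds ratio OR, the exposed risk is r = OR·b / (1 - b + OR·b), so the background share is b/r = [1 + b(OR - 1)] / OR. The values of b and OR are illustrative.

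| OR | b = 5% | b = 10% |
|---|---|---|
| 1.5 | 1.025/1.5 = 68% | 1.05/1.5 = 70% |
| 2 | 1.05/2 = 53% | 1.10/2 = 55% |
| 3 | 1.10/3 = 37% | 1.20/3 = 40% |

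**Step 3. Whether odds ratios fix the ranking.** Hold the odds ratios at 2 (sex) and 4 (other site) and overall detection at 15%. Solve for the reference risk p0 that gives 15% overall, then compute cell size × (cell risk - p0) / 0.15.

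- pS 20%, pA 30%: p0 = 7.9%. Sex only: 0.14 × (0.146 - 0.079)/0.15 = 6% of positives. Other site only: 0.24 × (0.255 - 0.079)/0.15 = 28%. Joint cell: 13%.
- pS 60%, pA 10%: p0 = 8.4%. Sex only: 0.54 × (0.155 - 0.084)/0.15 = 26%. Other site only: 0.04 × (0.268 - 0.084)/0.15 = 5%. Joint cell: 14%.

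The odds ratios are the same and the ranking is opposite, within the article's own exposure ranges.

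**Step 4. What strain typing can repair.** It is done in a subset, and footnote c names it for self-infection and persistence, not for sexual transmission. The Study population section expects 75% of women to be infected at both sites at inclusion. Where both sites started with the same type, a match fits persistence as well as self-infection.

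**The case against.** The case on the other side is substantial and rules out several stronger readings.

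- A reader might infer that only odds ratios will be reported. The article also says rates of incident detection will be calculated.
- A reader might infer that the planned effect estimates overstate transmission. They do not on this account: Model 2 compares each exposed category with no exposure, so its odds ratios are already relative to background. The fault lies in the labels. The article does not say that positives will be counted by label and presented as contributions.
- A reader might infer that every positive is assigned to a single cause. The joint cell is and/or, strain typing qualifies the labels, and the Definition of transmission section calls self-infection or persistence only likely, and only when types do not differ.
- A reader might infer that contributions cannot be obtained. The planned cell sizes and risks are enough to estimate them, apart from splitting the joint cell and subject to causal assumptions.
- The sources of background are not ignored. The semen biomarker is meant to catch unreported sex (in a subset, per Table 1). Viability and load are secondary outcomes, and the sensitivity analyses vary the outcome definition.
- The conflict over persistence is a tension, not a flat contradiction. All women were positive before treatment, and a positive after a negative sample could still be the old infection.

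It can also be said that post-estimation detail belongs in an analysis plan. That is fair for technique. But the aim, the effect measure and the interpretation column are all stated in this article, and as stated they do not fit together.

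**Conclusion.** The point holds in a limited form. The interpretation column credits background detections to transmission in the single-exposure cells, and strain typing only partly corrects this. *Persistence* is too narrow a label for an incident positive with no measured exposure. Odds ratios alone do not deliver the stated relative contributions.

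The firmest size is the null result: 28% to 72% of positives would carry a transmission label (26% to 58% in the single-cause cells alone) if neither exposure had any effect. It rests only on the article's exposure ranges and on independence. The background shares, such as 53-55% at an odds ratio of 2 with 5-10% reference risk, and the reversed ranking rest on assumed values and are illustrations. They also treat the odds ratio as a population-average one, whereas a mixed model gives a woman-specific one.

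**What to change.** 1. Present the Table 2 interpretations as possible causes, and rename the reference interpretation along the lines of: no measured exposure; residual or recurrent detection, or unreported sex. Reconcile this with the Definition of transmission section.
2. From the same Model 2, report the standardised risk per 2-week episode for each category, averaged over the random effect, with 95% confidence intervals. Add risk differences against no exposure beside the odds ratios.
3. Base any statement of relative contribution on the excess over the no-exposure risk, weighted by the observed exposure prevalence. Leave the joint cell unsplit.
4. State that other-site positivity at the same visit does not establish the direction of spread, so the site contribution is an association unless timing and typing support more.

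The cost is a reworded table column and post-estimation output from a model already planned; no new data or samples are needed.

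### Table 2 reads an unexposed anorectal detection as persistence without requiring that the anorectum was ever CT positive

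*Protocol article*

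**What the plan says.** Table 2 of the protocol article gives an interpretation for a positive test in each exposure category of Model 2. For the incident anorectal outcome, the unexposed row reads "No anorectal sexual exposure (at T_x_) AND genital CT negative (at T_x_ and T_x-2_) Persistence". It sets two conditions, on anal sex and on the genital test. It sets none on the earlier status of the anorectum.

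Study population expects a sizeable group to start without anorectal infection: "The majority (75 %) expectedly will have anorectal CT in combination with genital CT, and most of the remainder will have genital CT only". The same section gives the range "around 75-95 % of genital CT positive women also have anorectal CT".

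Treatment follows the routine test result. "Women who are anorectally tested in routine care and found anorectal CT positive are treated with a 7-day course of doxycycline", and "All other women receive a directly observed single dose of azithromycin 1000 mg".

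Definition of transmission treats persistence as a possible explanation when a positive sample follows a positive sample. For that situation it adds that "persistence is considered likely when CT strain types do not differ in a woman over time". Footnote c of Table 2 uses strain typing in two ways: agreement between sites supports self-infection, and agreement over time supports persistence. Footnote c of Table 1 limits typing to a subset.

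Numbers and power names women who are anorectally negative at inclusion among the reasons for recruiting 400. It does not say whether they are left out of the anorectal model.

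**The concern.** The study sets out to separate transmission from a partner, spread between a woman's own sites, and other reasons for detection after treatment. Model 2 is the table that attaches those explanations to the exposure categories. If the unexposed row is read as persistence for every woman, a first detection at a site with no recorded infection is explained as the survival of an infection that nobody observed there. The competing explanations (sex not recorded, earlier spread from the genital site, a false-negative earlier swab, a false-positive current swab) drop out of view.

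The Abstract gives treatment failure as the named example under the secondary objective, and the Treatment failure section says that the study should inform the debate on anorectal treatment. A reader who takes unexposed detections as persistence can easily go on to read them as failed treatment. The women to whom the label fits worst are almost all in one treatment group.

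**Working it through.** **Step 1. How many women could be affected.** Inputs: 400 women to be recruited (Numbers and power); 75-95% anorectal co-infection (Study population). Women anorectally negative at inclusion = N × (1 − co-infected share).

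- At 75%: 400 × 0.25 = 100.
- At 95%: 400 × 0.05 = 20.

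The upper figure is slightly generous, because a few women are expected to have anorectal infection only.

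**Step 2. Which treatment they receive.** Doxycycline requires a positive routine anorectal test. A woman with a negative anorectum at inclusion is therefore on azithromycin, unless her routine test was positive and her inclusion swab negative. The article does not state the treatment split, so a range is assumed. The lower end is a proxy from Setting: about 600 anorectal infections among 3718 CT-positive women, 600/3718 = 16%. The upper end is set at 50%.

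| Assumed doxycycline share | Azithromycin women | 100 negative at inclusion | 20 negative at inclusion |
|---|---|---|---|
| 16% | 335 | 100/335 = 30% | 20/335 = 6% |
| 50% | 200 | 100/200 = 50% | 20/200 = 10% |

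In the doxycycline group the share is about 0%. These are shares of women to whom the label could be misapplied, not shares of detections mislabelled. The article gives no rates from which the latter could be worked out.

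**Step 3. Apply the row to two hypothetical women.** Neither has anal sex in the episode, and both are genitally negative at the current sample and two weeks earlier.

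| | Anorectal results | Table 2 reading | Is persistence at the site supported? |
|---|---|---|---|
| A | Negative at inclusion and weeks 1, 2 and 4; positive at week 6 | Persistence | No earlier positive at this site |
| B | Positive at inclusion; negative at weeks 1 and 2; positive at week 4 | Persistence | Possible: an earlier positive exists |

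The row cannot tell A from B. In both, the positive sample follows a negative one, so neither strictly fits the account in Definition of transmission. In B an earlier infection at the site at least makes persistence tenable.

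**Step 4. Does strain typing separate them?** Eligibility requires genital and/or anorectal CT, so woman A was genitally positive at inclusion. Suppose her week 6 anorectal strain matches her genital strain at inclusion. The two samples come from different sites, so the match meets the self-infection criterion of footnote c. They also come from different times, so it meets the persistence criterion as well. The same finding supports both explanations. Where no typing is done, only the row label remains.

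**Step 5. Are these women removed elsewhere?** 400 × 0.75 = 300 and 400 × 0.95 = 380, which equals the 300-380 women with full retention that the article says it needs. This would fit a plan that deducts anorectally negative women. But the same sentence lists loss to follow-up, missing data and persistence as further allowances, and the match leaves no room for them. No exclusion is stated there, nor in Definition of transmission, the definition of alternate-site exposure or Statistical analyses.

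**The case against.** The strongest reply is that the column only interprets the reference category of a logistic model. Relabelling it changes no odds ratio, and no tally of persistence is planned. That is correct. A reader might infer that false persistence is tallied by treatment group and biases the treatment comparison. The article does not support this: the head-to-head comparison takes the woman, not the two-week episode, as its unit, and no use of Table 2's labels is specified for it.

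A second reply is that a between-site match points to self-infection under footnote c, and that the over-time criterion in Definition of transmission covers only detections that follow a detection. This also stands, so typing need not lead to a persistence reading for woman A. But it confirms that the Table 2 label goes further than that section does. Footnote c carries no such restriction, so the two criteria still overlap.

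Third, a reader might infer that these infections could not possibly have persisted. That is too strong. The inclusion swab may be a false negative, and Limitations concedes outcome misclassification. The supportable statement is that persistence at the site cannot be shown.

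Fourth, the women may be meant to be left out. Numbers and power leans that way, and at-risk rules can sit in a fuller document. Even so, the printed row would need that condition to be read correctly.

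**Conclusion.** The point holds as a fault in a stated interpretation rule. Followed literally, Table 2 attributes to persistence any unexposed first anorectal detection, including in the 20-100 of 400 women who may be anorectally negative at inclusion. That count rests on the article's own 75-95% range. That almost all of them receive azithromycin follows from its allocation rule. Only the percentages of the azithromycin group rest on an assumed treatment split.

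The regression estimates are untouched. What is exposed is the separation of persistence from transmission in the main analysis table, and any step from unexposed detections to treatment failure. The share of persistence readings that would be wrong cannot be determined from the article. The change should be made, but it is a correction of interpretation and not of the model.

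**What to change.** - In Table 2 Model 2, limit the persistence reading to sites with a positive result at that same site at inclusion or earlier in follow-up. Apply this to both outcomes.
- Label other unexposed incident detections as unexplained (unrecorded exposure, earlier spread from the other site, false-negative earlier swab, or false positive) and report them separately.
- In Definition of transmission and footnote c, confirm persistence by comparing strain types within the same anatomic site over time.
- State whether women anorectally negative at inclusion enter the anorectal model.

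The cost is a few lines of text and one derived flag from swabs already scheduled. Fewer detections will be labelled persistence, and one small category is added to the report.
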